## Methods/design

### Study design

The study is a multicenter randomized controlled trial comparing the effect of intensive early postoperative physiotherapy with the current standard of physiotherapy for patients undergoing elective THA for unilateral OA. General Hospital Novo mesto and Valdoltra Orthopedic Hospital are involved in the project, and the standard physiotherapy program for patients after THA is similar in both hospitals. All patients who will receive an anesthesiologist’s approval and will already be scheduled for surgery will be assessed for eligibility. An orthopedic surgeon will invite patients to participate and give oral and written explanations about the trial. Patients will be included in the study after signing a written informed consent form. After admission to the hospital, they will complete the routine preoperative outcome assessment questionnaires (Harris Hip Score (HHS) and 36-Item Short Form Health Survey (SF-36)) and have standard preoperative AP X-rays of both hips taken. Physiotherapists will perform the assessments: physical tests and an isometric muscle strength assessment. In both hospitals, the included patients will be randomized to either the intervention group (IG) or the control group (CG), and the surgeons and patients will be blinded to the randomization process. The procedure will be performed with the direct anterior approach only in the General Hospital Novo mesto by 1 surgeon and in the Valdoltra Orthopedic Hospital by 4 surgeons. Patients will be mobilized on the day of surgery. During the expected LOS of 2–5 days, all patients will receive current standard physiotherapy, oral analgesics, and cryotherapy. Patients in the IG will receive extra one-on-one training to learn strength and sensory-motor exercises. If the surgeon applies any limitations for a patient regarding rehabilitation after surgery, the patient will be excluded from the study. At discharge, patients in both groups will receive USB drives with exercise videos, written exercise instructions, and a training diary. Patients in the IG will also receive exercise aids for the strength and sensory-motor training. All patients will be followed up with regular phone calls concerning possible complications, completion of the training diary, and the clarity of the exercises. The patients will visit the hospital as usual after 1, 3, and 12 months following surgery. At each follow-up, the physiotherapists will perform assessments, and patients will fill out questionnaires. The patients will have a standard postoperative X-ray of the operated hip immediately after the surgery and AP X-rays of both hips after 1 year, so we will be able to compare measurements of the hip offsets of the operated and healthy hips and observe any changes regarding component position or osteolysis. At every follow-up, the surgeon and physiotherapist will ask the patient about any adverse effects or reasons for training cessation. The trial flowchart is displayed in Fig. 1.

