#### Randomization procedures

Randomization will be performed in each hospital separately. Randomization will be made using a bespoke web-based randomization protocol. Patients will be randomized on a 1:1 ratio to intervention group A (with strength and sensory-motor training included) or control group B (with standard-of-care physiotherapy), regarding inclusion order. Physiotherapists and coordinators of the trial will be aware of the randomization procedure. Patients and orthopedic surgeons will be blinded, but they will be unblinded, if any safety issue or adverse effect arises.

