#### Prescribed home-based strength and sensory-motor training

Before the patients are discharged, physiotherapists will teach patients in the IG special strength and sensory-motor exercises with exercise aids. The patients will also receive USB drives with special exercise videos, written exercise instructions, and a training diary to check performed exercises. The new training protocol includes exercises for improving hip stability and reducing local stresses on the hip prosthesis. In the training, we considered safety regarding hip and lumbar spine load, falls, and prosthesis luxation. Training will consist of hip muscle strengthening exercises (focusing on the abductors), hip and pelvic stabilization exercises, ankle and knee muscle strengthening exercises (for improved dissipation of impact forces and femoral inner rotation control), and trunk muscle strengthening exercises (for stabilization of the pelvis and lumbar spine and a reduction in local loads). We ensured the exercises are simple and easy to understand, the videos that are to be watched at home are easy to follow, and the training program does not require expensive equipment. In the first two postoperative weeks, the focus is on learning the proper exercise technique and developing a sense of loading. Patients will watch special instructional short videos with exercise descriptions. Each exercise will be demonstrated with easy and challenging options as well as oral and written instructions. We will use a revised Borg category-ratio scale (0 to 10 scale) for perceived exertion to monitor and guide exercise intensity [33]. In sets of fluent concentric repetitions of movements (10–12 repetitions per set), the rating of perceived exertion will be recorded for the last repetition. When holding an isometric position, the rating will be recorded for the end of the interval (with a lengthening of the interval to 30 s, until we can achieve desired perceived exertion at the end of the interval). In sets of isometric contractions, every repetition will be made with the maximal voluntary effort exerted for 6 s (2 s for force increments and 4 s for maintenance). The implementation of fluent concentric movements is intended to increase muscle mass and improve physical endurance, while maximal isometric contractions are used for improving the level of muscular activation [34]. Exercises with isometric trunk positions will be prepared with recommendations for isometric trunk stabilization training [35]. These concepts collectively allow for individual load adaption for every exercise regarding individual patient abilities and load progression in accordance with his or her progress in muscle strengthening training [34]. Each session consists of a warm-up with 2 options (5–7 min of toe walking on the same spot or step-ups on a 10-cm tall step), strength training for both legs (30–40 min; 11 exercises; 1–4 fluent concentric repetitions of the single-leg squat and lying side hip raise; 5–8 maximal isometric contractions of the sitting ball squeeze, seated elastic band hip abduction, and diagonal ball push into the opposite thigh; 9–11 holds in the isometric positions, side plank, and bridge), and stretching (standing hip flexor stretch, sitting forward bend stretch, standing lateral trunk stretch). Strength training will be performed twice weekly, with a minimum of 2 days of rest. Until the 5th postoperative week, perceived exertion will be increased on the Borg scale from 5 to 8, and then it will be increased to 9 until the assessment at 3 months. In the first 5 postoperative weeks, 2 sets of each exercise will be recommended, and after these 5 weeks, 3 sets will be recommended. Sensory-motor training will be added to strength training to increase muscular activation and rate of force development and will be practiced on the days without strength training [36]. Exercise for ankle stability will be performed with a one-dimensional wooden balance board in the frontal and sagittal plane [37]. At the beginning, patients will perform 6 sets for each leg and 12 sets after the 7th postoperative week. The intensity of the exercise will be increased according to patient abilities with changes in the stability of the balance board. For every exercise, severe pain will be a reason for training cessation and contact with the physiotherapist.

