#### Maximal voluntary isometric contractions

We use a specially prepared measuring device with a dynamometer attached to stiff band metal chains, prepared similarly to those in Roussel et al. and Essendrop et al. [38, 39]. The ICC for a similar device, used by one of the senior authors for lumbar muscle strength assessment, is > 0.94. For the assessment of maximal isometric strength, a maximal voluntary isometric contraction for 6 s is used. The same procedure of obtaining a maximal voluntary contraction is used for every strength measure. Movement is assessed in 3 planes for the trunk (extension, left and right abduction) and operated hip (flexion, extension, and abduction), and movement is assessed in 2 planes for the contralateral hip (extension, abduction). All strength tests are performed in a neutral standing position, and the patient rotates on the measuring device so that the exerted force is always in the direction opposite of the dynamometer. Before the measurements, the height of pelvic support is set to the reference point of the iliac crest of each patient. Patients are verbally encouraged to generate maximal effort. The mean duration of the complete test is 20 min. We wrap the band around the trunk under the armpits for trunk tests and around the ankle for leg tests. We measure the height of pelvic support, maximal contraction force, and distance between the upper border of the support board and the middle point of the stiff band. All measurements are taken twice.

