#### Questionnaires

##### Harris Hip Score

The HHS is a widely used disease-specific measure of hip disabilities after THA. The physiotherapist administers the test in the form of a structured interview with the patients. The domains include pain, functions of daily living, and gait. The rating scale is from 0 (worse) to 100 points (best) [40]. The HHS is considered to have good validity and reliability [41].

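### Patients are said to be blinded to an intervention they can see, and the primary outcome tests are assigned to physiotherapists, a group that knows the allocation and teaches the intervention

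*Protocol article*

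**What the plan says.** **Blinding.** Randomization procedures says "Patients and orthopedic surgeons will be blinded, but they will be unblinded, if any safety issue or adverse effect arises". The sentence before it says "Physiotherapists and coordinators of the trial will be aware of the randomization procedure". Study design words the blinding of patients and surgeons differently: "the surgeons and patients will be blinded to the randomization process".

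**What each arm receives.** Patients are invited with an oral and written explanation of the trial (Study design). All then have standard physiotherapy. The intervention group has additional one-to-one training in hospital, and "Patients in the IG will also receive exercise aids for the strength and sensory-motor training". Its videos show the special exercises, which use balls, an elastic band and a balance board (Prescribed home-based strength and sensory-motor training). Controls go home with videos of the standard exercises, written instructions and a diary (Standard rehabilitation).

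**Who teaches and who tests.** Before discharge, "physiotherapists will teach patients in the IG special strength and sensory-motor exercises with exercise aids". Study design says "At each follow-up, the physiotherapists will perform assessments, and patients will fill out questionnaires", and the Abstract names the physical tests and the isometric strength test as the physiotherapists' task at baseline and at 1, 3 and 12 months. Outcome measures lists the 10-m walk, the 8-foot Up and Go and isometric strength as the primary outcome. For the strength test, "Patients are verbally encouraged to generate maximal effort".

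**Harris Hip Score.** The Abstract and Study design have patients complete it. Its own section says "The physiotherapist administers the test in the form of a structured interview with the patients".

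**The concern.** Blinding is a property that readers use to grade a trial. If patients are described as blinded when they know their arm, the report overstates the protection against bias in what patients put into the tests and how they answer the questionnaires.

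The second issue is who measures. The primary outcome consists of performance tests, and a maximal voluntary contraction depends directly on the effort a patient is brought to make. A tester who knows the arm, and may have taught the patient the exercises, can encourage differently without intending to. Any such difference enters the treatment comparison as a systematic shift.

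**Working it through.** The point carries no figure of its own, so the check is mainly a comparison of sections.

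**Step 1. Can patients be unaware of their arm?**
- Patients are told about the trial before consent, and it compares intensive with standard physiotherapy (Study design).
- Extra one-to-one teaching, exercise aids and special exercise videos go to the intervention group only (Study design; Prescribed home-based strength and sensory-motor training).
- Both groups receive a USB drive, written instructions and a diary, so these items do not reveal the arm by themselves. The additional teaching and equipment do.
- Result: a patient can readily infer the arm before discharge. Blinding to arm is not achievable with this intervention.

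**Step 2. Does the Study design wording rescue the claim?** Being blinded to the randomization process could mean that the sequence is concealed until assignment. But Randomization procedures provides for patients to be unblinded later, after a safety issue or adverse effect. Only someone still unaware of the arm can be unblinded at that stage. The two sections therefore make different claims, and the stronger one fails at Step 1.

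**Step 3. Who is aware, who teaches, who tests?**

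| Role | Assigned to | Section |
|---|---|---|
| Aware of the randomization | Physiotherapists, coordinators | Randomization procedures |
| Teaches intervention exercises | Physiotherapists | Prescribed home-based strength and sensory-motor training |
| Performs the physical and strength tests | Physiotherapists | Abstract; Study design |
| Asks about adverse effects and reasons for stopping training | Surgeon and physiotherapist | Study design |

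All the primary outcome tests fall to a professional group the plan makes aware of the randomization. No masked tester is named, and no rule separates teacher from tester. The questions on adverse effects and training, asked at the same visits, could reveal the arm to a tester who did not already know it.

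**Step 4. Where is encouragement described?** Only under Maximal voluntary isometric contractions. That section says the same procedure for obtaining a contraction is used for every strength measure, but gives no fixed wording for the encouragement.

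**Step 5. Does this touch the sample size?** Inputs from Sample size calculation: difference 0.10 m/s, SD 0.28 m/s, 5% significance, 80% power; two-tailed testing from Data management and analysis.
- n per group = 2 × (1.960 + 0.842)² × 0.28² / 0.10² ≈ 123.1, rounded up to 124. The stated 124 per group is reproduced, with power 80.3%.
- Standard error of the difference = 0.28 × √(2/124) = 0.0356 m/s.

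A larger sample would shrink this standard error but leave a systematic measurement difference where it is. The sample size needs no change on this account.

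**The case against.** **Concealment, badly worded.** The strongest defence is that the authors meant concealment of the sequence. Study design reads that way, and so does the statement that physiotherapists are aware of the randomization procedure. This is plausible as intent, but it does not fit the unblinding clause. What stands is that the remedy is to reconcile two sections; no misconduct is implied.

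**Staffing detail.** A journal article may leave staff assignment to the full protocol. A reader might infer that the same individuals teach and test. The document names only the professional group, so that is not established. What it does say is that the testing group is aware of the randomization.

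**Stronger readings that the document does not support:**
- That patients are encouraged during the 10-m walk or the 8-foot Up and Go. Encouragement is described for the strength test only, and the article does not say whether the walk is at usual or maximal pace.
- That surgeon unblinding biases the primary outcome. Surgeons perform none of those tests, unblinding for safety is not a defect, and nothing shows more adverse effects in the intervention arm.
- That the bias amounts to a particular number of m/s. Nothing in the document anchors one.
- That Data management and analysis also makes the Harris Hip Score patient-completed. It speaks of questionnaires without naming that score.

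**Feasibility.** The number of physiotherapists per site is not given, and all of them may know the allocation, so a rota may not yield a masked tester. This stands, and the fix is conditional for that reason. It also rules out relying on a sensitivity analysis by tester awareness: if every tester knows the arm, there is no variation to analyse.

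**Conclusion.** The statement that patients are blinded is wrong as written and conflicts with the narrower wording in Study design. This follows from the document alone and needs no assumption beyond patients noticing the extra teaching and equipment they are given.

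All primary outcome testing is assigned to a group that is aware of the randomization and teaches the intervention, with no masked tester stated. The exposure is clearest for isometric strength, where encouragement is part of the procedure. Whether bias occurs, and how large it would be, cannot be determined from the document.

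A reader might go further and conclude that the trial is invalid. That does not follow: randomization and the comparison of arms remain sound for a trial reported as open-label for patients. The Harris Hip Score discrepancy is secondary, but it matters here because an interview by an aware physiotherapist would expose that score to the same influence.

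**What to change.** 1. **Correct the claim.** Replace the statement on patient blinding in Randomization procedures with one that patients and treating physiotherapists are not blinded. Describe allocation concealment separately, align Study design with it, and report the trial as open-label for patients.
2. **Separate tester from teacher where existing staffing at each site allows.** Tests should be done by a physiotherapist who did not teach that patient and is not shown the allocation or the diary, and before the diary review and the adverse-effect questions. Where this is not possible, report assessment as unblinded.
3. **Standardize encouragement.** Use one fixed script for the strength test in both arms.
4. **Reconcile the Harris Hip Score.** State the mode actually used, the same in both arms, and correct whichever sections disagree. The document gives no basis for preferring one mode.

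**Cost.** Items 1 and 4 are wording; item 3 is a short written script. Item 2 brings some scheduling inconvenience and may not be achievable at a site with few physiotherapists. Recruitment began in 2018 and was still open at submission (Trial status), so changes to testing reach only later visits. Measurements already taken remain under the existing procedure, and the report should say when the procedure changed.

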#### Sample size calculation

A power calculation was performed based on a clinically significant difference in gait speed of 0.10 m/s on the 4- or 10-m walk (10 MW) test using data from Perera et al. [32]. Based on a substantial meaningful change of 0.10 m/s between the interventional and control groups and standard deviation of 0.28 m/s, with a significance level of 5% and a power of 80%, a needed sample size of 124 patients in each group was estimated (248 patients in total). All patients from surgeons, participating in the study, will be assessed for eligibility. A total of 124 patients in each hospital will be randomized according to the procedure described above on a 1:1 ratio, so that there will be 62 patients in group A and group B in both hospitals.

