Before any statistical analysis, data will be tested for normal distribution using the Kolmogorov–Smirnov test (K–S test). With normally distributed variables, the analysis of variance for repeated measures (AnovaRM) with two factors (time × group) will be employed. It will test the differences in the effects of two different exercise protocols. AnovaRM will be used to analyze between-group differences in the score changes among all time points, represented by preoperative measurements (on admission to the hospital) and measurements 1, 3, and 12 months postoperatively. Afterwards, the initial AnovaRM, post hoc tests with AnovaRM (time × group) with two time points will be performed. Differences between all pairs of time points will be analyzed. Additionally, the paired samples *t*-test to test for in-group differences in the score changes between the pairs of time points and the independent samples *t*-test for between-group comparisons at the same time point will be calculated. The bivariate Pearson correlation will be calculated for testing the relationships between variables representing relative changes in the results between two different time points (e.g., post-treatment/baseline) for each group separately. To test the reliability of maximal voluntary isometric contraction measurements and the 8UG test, we will use the intraclass correlation coefficient (ICC) with the two-way mixed-effects model with absolute agreement. Data will be presented as the arithmetic mean and standard deviation. In the case of a non-normal distribution, data will be presented as the median and interquartile range, and nonparametric tests will be used respectively for comparisons of dependent and independent groups. Instead of AnovaRM, the nonparametric marginal model (nparLD, R-statistics) [47] will be used. T-tests for dependent and independent samples will be changed with Wilcoxon matched-pair signed-rank test and Mann–Whitney *U* test, respectively. The Pearson correlation will be substituted with the Spearman rank correlation. Adverse effects comparison among the two groups will be made by using the chi-square test. We will consider a *P* value less than 0.05 as significant for all measures and use a 95% confidence interval (CI). A significance level (alpha) of 0.05 will be tested with a two-tailed test.

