## Trial status

Patient recruitment for our study commenced in January 2018 in the General Hospital Novo mesto and in April 2018 in the Valdoltra Orthopedic Hospital and is on-going at the time of the manuscript submission. The expected time of recruitment completion was June 2021, but was postponed due to COVID-19.

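### The 124 per group needed for 80% power is also the number randomised, so the stated power has no reserve against exclusions and losses after randomisation

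*Protocol article*

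**What the plan says.** The Sample size calculation section of the protocol article gives the planning inputs, "Based on a substantial meaningful change of 0.10 m/s between the interventional and control groups and standard deviation of 0.28 m/s", and the result, "with a significance level of 5% and a power of 80%, a needed sample size of 124 patients in each group was estimated", which makes 248 in total. The sidedness comes from the Data management and analysis section: "A significance level (alpha) of 0.05 will be tested with a two-tailed test".

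The same sample size paragraph then sets recruitment at 124 patients per hospital, split evenly, "so that there will be 62 patients in group A and group B in both hospitals". It mentions no allowance for loss and no replacement of patients who leave.

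Three other places bear on how many of those patients can be analysed:

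- **Study design** describes randomisation, then the operation, and then says that if the surgeon imposes restrictions on rehabilitation, "the patient will be excluded from the study".
- **Exclusion criteria** include discharge to an institution instead of home, which is settled only at the end of the hospital stay.
- **Study design** schedules visits at 1, 3 and 12 months, and **Objectives** names both 3 months and 1 year.

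The Data management and analysis section promises an intention-to-treat analysis, with sensitivity analyses where data are missing.

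**The concern.** A sample size formula returns the number of patients who must contribute an outcome. Here that number and the number to be randomised are the same, although the design itself provides ways for patients to leave after allocation. The 80% then describes a trial in which nobody leaves.

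A fuller document could not simply fill this gap. The article fixes both numbers, and they are equal, so an allowance stated elsewhere would contradict this section.

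At stake is how the planned power is read. If gait speed shows no difference, readers will judge the result partly against a claimed 80% chance of detecting 0.10 m/s. For the comparison used in the calculation, that chance would be lower by an amount that depends on losses the protocol does not estimate.

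**Working it through.** **Inputs**

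- Difference δ = 0.10 m/s, SD σ = 0.28 m/s, power 80%: Sample size calculation.
- α = 0.05, two-sided: Sample size calculation, and Data management and analysis.
- Allocation 1:1: Randomization procedures.
- Loss rate: not stated. The values 5%, 10%, 15% and 20% below are assumptions.

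**Step 1: reproduce the plan's figure**

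n per group = 2 × (1.960 + 0.8416)² × (0.28 / 0.10)² = 123.07, rounded up to 124.

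The exact two-sample t-test solution is 124.04 per group. A one-sided test would need 97. The stated 124 is therefore the two-sided figure with no inflation for loss.

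**Step 2: count the patients randomised**

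62 per arm per hospital × 2 hospitals = 124 per arm, and 2 × 124 = 248 in total. Needed minus randomised is zero.

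**Step 3: power as the number analysed falls**

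Normal approximation: power = Φ( δ / (σ × √(2/n)) − 1.960 ).

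At n = 124: 0.10 / (0.28 × √(2/124)) = 2.812; 2.812 − 1.960 = 0.852; Φ(0.852) = 80.3%.

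At n = 112: 0.10 / (0.28 × √(2/112)) = 2.673; 2.673 − 1.960 = 0.713; Φ(0.713) = 76.2%.

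The last column uses the noncentral t distribution. Numbers analysed are 124 × (1 − loss), rounded to the nearest whole patient.

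| Lost or excluded (assumed) | Analysed per group | Power, normal | Power, exact t |
|---|---|---|---|
| none | 124 | 80.3% | 79.99% |
| one per group | 123 | 80.0% | 79.7% |
| 5% | 118 | 78.3% | 78.0% |
| 10% | 112 | 76.2% | 75.8% |
| 15% | 105 | 73.5% | 73.1% |
| 20% | 99 | 71.0% | 70.6% |

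**Step 4: do losses after allocation follow from the text?**

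The intervention group is taught its exercises during the hospital stay, so allocation must be known before discharge. An exclusion based on discharge destination therefore falls after randomisation. The exclusion for surgical restrictions also falls after randomisation if events run in the order that Study design narrates them. Ordinary loss over 12 months comes on top. The text does not say how large any of these will be.

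**The case against.** **The table covers only one comparison.** It applies to an unadjusted comparison of two means at one visit. The main planned analysis is a repeated-measures ANOVA (time × group), followed by tests on pairs of time points, which compare change. Their power depends on the correlation r between visits, which the protocol does not give. If 0.28 m/s is the SD at each visit (an assumption), the SD of change is 0.28 × √(2(1 − r)). With 10% loss, normal-approximation power is then about 68% at r = 0.4, 76% at r = 0.5, 85% at r = 0.6 and 93% at r = 0.7. This objection stands. A reader might infer that 80% is a ceiling, or that the trial cannot reach it. The documents do not support that, because an analysis using baseline could do better or worse. The protocol did not size the trial on such an analysis, however, so the objection does not support the stated 80% either.

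**Patients missing one visit are not necessarily lost.** A reader might infer that the analysis discards anyone with an incomplete set of visits. The plan does not say so. It also includes t-tests at each visit and two-visit comparisons, which need only the visits compared.

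**The loss may be small.** One lost patient per group costs about 0.3 points, and 5% costs about 2 points. The calculation is tied to no visit, and the Discussion expects the largest differences at month 3, when cumulative loss can be no greater than at month 12. This stands as a limit on size.

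**Intention-to-treat is planned.** It keeps patients in their allocated group, and sensitivity analyses probe assumptions about missing values. Neither restores the information in outcomes that were never measured.

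**The pandemic.** A reader might take the remark in Trial status that completion of recruitment "was postponed due to COVID-19" as evidence of attrition. It reports a recruitment delay and says nothing about the number analysed.

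**Conclusion.** The point holds in a limited form. The arithmetic is right: 124 per group is correct for the stated inputs. The weakness is that the number needed and the number randomised coincide, while the protocol provides for exclusions after surgery and at discharge and for follow-up to 12 months.

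For the unadjusted comparison on which the calculation rests, 80% power requires essentially all 248 patients to be analysed. The shortfall is trivial for a handful of losses and becomes material from about 5–10%: 2 points at 5%, about 4 at 10%, 7 at 15% and 9 at 20%.

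This conclusion rests on the assumed loss rates, on an SD of 0.28 m/s, and on an unadjusted test at a single time point. It does not show that the trial is invalid, or that every planned analysis has less than 80% power.

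**What to change.** Recruitment began in 2018, and the trial need not be enlarged. Restate the figure in the Sample size calculation section, for example:

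*Randomising 248 patients gives 80% power if all are analysed, and about 78%, 76%, 73% and 71% if 5%, 10%, 15% and 20% are lost or excluded (assumed rates), for an unadjusted comparison at one time point.*

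If the sponsor has an expected loss rate covering both the exclusions after randomisation and drop-out, it should replace the assumed range.

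The cost is one sentence and a slightly less favourable power statement. Nothing in the design, conduct or analysis changes.

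For comparison, keeping 124 analysed per group by over-recruiting would take 124 / 0.90 = 137.8, so 138 per group (276 in total), at 10% loss, and 124 / 0.80 = 155 per group (310 in total) at 20%. That is not what is asked for here.
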